**How to Measure Thickening and Redness and skin damage**

Check for hardness or thickening (induration), redness (erythema) and skin damage (vesicles, ulcers) at injection site on Day 1, 2 and 3 after each injection. (Day 1, 2 and 3 are 24, 48, and 72 hours after study vaccination respectively).

If you see any thickening, redness, or lump at the injection site, use the measuring tape provided to measure the WIDEST part of the response on Days 1, 2, and 3.

Record the result rounded to the *nearest 10*, for example, 0, 10, 20, or 30.

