No more than one volunteer per day will be enrolled for the first four volunteers to receive electroporation in each dose group. For these four volunteers, an additional telephone call to assess safety and adverse events will be made on the day following vaccination. If four vaccinations by electroporation have occurred without greater than moderate adverse events, the remainder of the group can be enrolled with no fixed interval between volunteers.

A. **Description of Adverse Events (AE) Detection and Reporting:**

**i. Adverse Event Definition**: An adverse event is any noxious, pathologic, or unintended change in anatomical, physiologic, or metabolic functions, as indicated by physical signs, symptoms, and/or laboratory changes occurring in any phase of the clinical trial, whether associated with drug and whether or not considered drug related. All of the following are to be considered adverse events:

- An exacerbation of a pre-existing condition.
- An inter-current illness.
- Any drug interaction.
- Any event related to a concomitant medication.
- Development of an abnormal laboratory value or a significant change from baseline in a laboratory value within the range of normal, considered by the investigator to be clinically important.

Any adverse event prior to the first vaccination will be reported as a pre-existing condition on the “previous conditions” source document. At each outpatient visit, subjects will be questioned and/or examined by the PI or his designee for evidence of AEs. The onset and end dates, severity and relationship to study vaccine and EP device will be recorded in the medical record for each event.

**ii. Assessment of Severity:** The severity of the AE will be assessed according to the Adverse Event Severity Assessment Table (see Appendix C).

**iii. Serious Adverse Event (SAE) Definition:** An SAE is an AE that results in any of the following outcomes.

- Death
- Life threatening condition
- Hospitalization or prolongation of stay
- Persistent or significant disability or incapacity
- Congenital anomaly or birth defect
- Medically significant event, including laboratory abnormalities

Important medical events that do not result in death, are life threatening, or require hospitalization, may be considered SAEs when, based on appropriate medical judgment, they may jeopardize the volunteer, or may require medical/surgical intervention to prevent one of the outcomes listed in this definition.

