**APPENDIX C: ADVERSE EVENT SEVERITY ASSESSMENT TABLE**

| **PARAMETER** | **MILD** | **MODERATE** | | **SEVERE** | |
| --- | --- | --- | --- | --- | --- |
| **General Principle for Severity Assessment** | Mild discomfort. Minimal or no limitation of daily activity.  No need for medical intervention. | Moderate discomfort.  Some limitation of daily activities (e.g. able to work part-time)  May require minimal or no medical intervention | | Severe discomfort. Marked limitation of daily activities (e.g. unable to work). Requires medical intervention. | |
| **LOCAL REACTOGENICITY:** | | |  | |  |
| **Pain and tenderness** | Minimal discomfort associated with minimal or no limitation of use of arm | Moderate discomfort with some limitation of use of arm causing some interference with daily activities. May require single dose of analgesic or NSAID. | | Severe discomfort with significant limitation of use of arm causing marked limitation of daily activities (e.g. unable to work). Requires medical intervention (e.g. repeated doses of analgesic or NSAID). | |
| **Erythema (redness) or skin discoloration** | Light red blush up to 25% of the circumference of the upper arm | Marked redness involving up to 50% of the circumference of the arm | | Brick red involving >50% of the circumference of the upper arm | |
| **Edema (swelling)** | Light edema involving up to 25% of the circumference of the upper arm | Marked edema involving up to 50% of the circumference of the arm | | Significant edema >50% of the circumference of the upper arm | |
| **Induration** | Hardening under the skin <1.5 cm in diameter | Hardening under the skin 1.5-3.0 cm in diameter | | Hardening under the skin >3.0 cm in diameter | |
| **Skin damage (vesicle, ulcer)** | Vesicles or superficial disruption of epithelium < 1 cm | Vesicles or superficial disruption of epithelium 1-2 cm | | Full thickness disruption of the epithelium (ulceration) > 2 cm | |
| **Formation of crust, scab or scar** | Crust, scab or scar = 2cm | Crust, scab or scar 2­4cm | | Crust, scab or scar > 4cm | |

| **SYSTEMIC REACTOGENICITY** | |  |  |
| --- | --- | --- | --- |

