| **Vomiting** | Minimal nausea causing no interference with daily activities | Moderate nausea causing some interference with daily activities. | Significant nausea causing marked limitation of daily activities (e.g. unable to work). Requires medical intervention |
| --- | --- | --- | --- |
| **Pruritus** | Localized itching at vaccination site | Itching at the injected arm (beyond vaccination site) | Generalized itching |
| **Rash** | Localized maculopapular (non­urticarial) rash at the vaccination site area causing no interference with daily activities | Diffuse maculopapular (non-urticarial) rash at the injected arm (beyond vaccination site) causing some limitation of daily activities | Systemic maculopapular (non­urticarial) rash causing marked limitation of daily activities. Requires medical intervention |
| **Allergic reaction** | Localized urticaria at vaccination site causing no interference with daily activities | Diffuse urticaria at the injected arm (beyond vaccination site) and causing some limitation of daily activities | Systemic urticaria or angioedema causing marked limitation of daily activities. Requires medical intervention |
| **HEMATOLOGY** |  |  |  |
| Hemoglobin | 10.0 g/dL – 11.0 g/dL OR  any decrease = 2.5 g/dL | 9.0 g/dL – 9.9 g/dL OR  any decrease = 3.5 g/dL | = or <8.9 g/dL  OR  any decrease = 4.5 g/dL |
| WBC—Elevated WBC—Decreased | 13,000–14,999/mm3 | 15,000–19,999/mm3 | = or >20,000/mm3 |
| 2000–2499/mm3 | 1500–1999/mm3 | = or <1499/mm3 |
| Absolute Neutrophil Count | 1000–1300/mm3 | 750–999/mm3 | = or <749/mm3 |
| Absolute Lymphocyte Count | 600–649/mm3 | 500–599/mm3 | = or <499/mm3 |
| Absolute CD4 Count (HIV Negative) | 300–400/mm3 | 200–299/mm3 | = or <199/mm3 |
| Platelets—Decreased Platelets—Elevated | 100,000–124,999/mm3 | 50,000–99,999/mm3 | = or <49,999/mm3 |
| NA | 550,000–600,000/mm3 | > 600,000/mm3 |
| **CHEMISTRY** |  |  |  |
| BILIRUBIN (total) | 1.0–1.5 x ULN | >1.5–2.5 x ULN | >2.5 x ULN |
| CREATININE | 1.1–1.3 x ULN | >1.3–1.8 x ULN | >1.8 x ULN |
| AST (SGOT) | 1.51–3.0 x ULN | >3.0–6.0 x ULN | >6.0 x ULN |
| ALT (SGPT) | 1.51–3.0 x ULN | >3.0–6.0 x ULN | >6.0 x ULN |
|  |  |  |  |

| **URINALYSIS** | | |  | |  |
| --- | --- | --- | --- | --- | --- |
| PROTEINURIA | 1+ (30 mg/dL) | 2–3+ (100-500mg/dL) | | 4+ (> 500mg/dL) | |
| Random urine 24-hour urine | 200 mg–500 mg loss/day | > 500 mg–1.0 g loss/day | | > 1.0g loss/day | |

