**APPENDIX D: Volunteer Diary Card**

**Volunteer Diary Card**

**Protocol DHO-0614-0707**

Volunteer ID Number

Date and time of injection

Date of Next Visit:

Name of Study Contact:

24 HOUR EMERGENCY telephone number to report any unusual or severe symptoms that occur before the next visit:

** Please bring this card to your next clinic visit.

If you experience any symptoms following this vaccination that persist beyond day 3 (72 hours) please indicate the severity for each one noted in the column under the day you noticed the symptom. Unless an item says MEASURE, please rate severity as “-“for none, “+” for mild, “++” for moderate, or “+++” for severe.

| **Code** | **Meaning** |
| --- | --- |
| - | Symptom not present |
| + | Mild: Transient or mild discomfort, no limitation in normal daily activity |
| ++ | Moderate: Some limitation in normal daily activity |
| +++ | Severe: Unable to perform normal daily activity |

| **Possible Symptoms** | **Date** | **Date** | **Date** | **Date** | **Date** | **Date** | **Date** |
| --- | --- | --- | --- | --- | --- | --- | --- |
| Local Symptoms  Pain (pain without area being touched) at injection site |  |  |  |  |  |  |  |
| Tenderness (pain when area being touched) at injection site |  |  |  |  |  |  |  |
| Redness (erythema) at injection site  MEASURE | mm | mm | mm | mm | mm | mm | mm |
| Skin damage (vesicles, ulcers) at injection site  MEASURE | mm | mm | mm | mm | mm | mm | mm |
| Hardness or thickening (induration) at injection site MEASURE | mm | mm | mm | mm | mm | mm | mm |
| Swelling (edema) at injection site |  |  |  |  |  |  |  |
| Formation of crust, scab or scar MEASURE | mm | mm | mm | mm | mm | mm | mm |
| Systemic Symptoms  Headache |  |  |  |  |  |  |  |
| Chills |  |  |  |  |  |  |  |
| Nausea |  |  |  |  |  |  |  |
| Vomiting |  |  |  |  |  |  |  |
| Temperature MEASURE  Measure before midnight of the date stated | °F | °F | °F | °F | °F | °F | °F |
| Feeling of general discomfort, uneasiness, a general sick feeling (malaise) |  |  |  |  |  |  |  |
| Muscle aches (myalgia) |  |  |  |  |  |  |  |
| Aching joints (arthralgia) |  |  |  |  |  |  |  |

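### Rounding diary sizes to 10 mm moves lesions just above a severe cut-off to moderate, and diary redness and swelling are not on the Appendix C grading scale

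*Protocol*

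**What the plan says.** Primary Endpoints lists severe local reactogenicity first, and names erythema, edema, skin damage, induration and crust or scab among its components. The proportion with mild and moderate reactions is a further primary endpoint. Under Assessment of Severity in the Data and Safety Monitoring Plan, severity "will be assessed according to the Adverse Event Severity Assessment Table (see Appendix C").

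Appendix C grades induration by diameter: moderate is "Hardening under the skin 1.5-3.0 cm in diameter" and severe is "Hardening under the skin >3.0 cm in diameter". Skin damage has size cut-offs at 1 and 2 cm, and severe also requires full-thickness disruption. Crust, scab or scar has cut-offs at 2 and 4 cm. Erythema and edema are graded by share of upper-arm circumference, at 25% and 50%. Erythema also carries a colour descriptor; its severe grade is "Brick red involving >50% of the circumference of the upper arm".

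The diary marks redness, skin damage, induration and crust as items to measure in mm. The item "Swelling (edema) at injection site" has no such mark and no mm cells, so it is rated by how far it limits daily activity. Volunteers who see thickening, redness or a lump are to "use the measuring tape provided to measure the WIDEST part of the response on Days 1, 2, and 3" and then to "Record the result rounded to the *nearest 10*, for example, 0, 10, 20, or 30".

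**The concern.** The diary and the grading table were built on different scales. For induration, skin damage and crust the unit is the same, but the diary's resolution is too coarse for a table whose severe cut-offs fall exactly on multiples of 10 mm with a strict inequality. Rounding then acts in one direction at the boundary that defines a severe event. For redness and swelling the unit itself differs: a width in mm or an activity code cannot be turned into a percentage of arm circumference, and the protocol schedules skin-fold thickness but no circumference.

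The line between moderate and severe matters here. It defines the first primary endpoint. It also enters the release of each dose group after its first four electroporation volunteers, the removal of a volunteer for a severe injection reaction, and the three-volunteer suspension rule. With 8 volunteers per arm, one changed grade moves an arm's severe rate by 1/8 = 12.5 percentage points.

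**Working it through.** The protocol gives no figure to reproduce on this point. The check applies the diary rule to every whole-mm size from 1 to 60 and compares the Appendix C grade before and after.

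**Inputs.** Rounding rule and mm columns: Volunteer Diary Card and its measuring instructions. Cut-offs: Appendix C. Assumption: halves round up. Assumed upper-arm circumference 250-400 mm, because the documents give none.

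**Rounding.** Recorded size = 10 × floor(size/10 + 0.5).

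| Sign (size part only) | True size | Recorded | Grade, true to recorded |
| --- | --- | --- | --- |
| Induration (15, >30 mm) | 31-34 mm | 30 mm | severe to moderate |
| Skin damage (10, >20 mm) | 21-24 mm | 20 mm | severe to moderate |
| Skin damage | 5-9 mm | 10 mm | mild to moderate |
| Crust, scab or scar (>20, >40 mm) | 41-44 mm | 40 mm | severe to moderate |
| Crust, scab or scar | 21-24 mm | 20 mm | moderate to mild |
| Any of the three | 1-4 mm | 0 mm | mild to no recorded size |

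All other sizes keep their grade. The 15 mm induration cut is unaffected (14 becomes 10, mild; 15 becomes 20, moderate).

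- At the severe cut-offs the largest moderate sizes, 30, 20 and 40 mm, round to themselves, so nothing moves from moderate to severe.
- The downward band is less than 5 mm wide. Induration of 35 mm or more, skin damage of 25 mm or more and crust of 45 mm or more stay severe.
- At the lower cut-offs the error goes both ways.

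**Erythema.** The 25% threshold is 0.25 × 250 = 62.5 mm to 0.25 × 400 = 100 mm. The 50% threshold is 0.50 × 250 = 125 mm to 0.50 × 400 = 200 mm. A diary entry of 150 mm, even if it ran around the arm, is 150/250 = 60% on the smaller arm (above the severe limit) and 150/400 = 37.5% on the larger (within the moderate band). One recorded value therefore has no fixed grade. Rounding is minor here: 5 mm is 5/250 = 2.0 to 5/400 = 1.25 percentage points. The widest part may also run along the arm, and colour is not recorded.

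**Swelling.** No size is recorded, so no percentage can be derived.

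**Is there another record?** Staff record local reactions at 30-45 minutes, telephone 1 to 4 days after each vaccination, and next see the volunteer at week 1. For Days 1 to 3 the diary is the only scheduled size measurement.

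**After the change.** With whole-mm recording, every size from 1 to 60 mm keeps its grade for induration, for crust and for the size part of skin damage. Erythema and edema are not repaired by this alone.

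**The case against.** A reader might infer that severe local reactions are systematically recorded as moderate. The documents do not support that: only lesions less than 5 mm above a cut-off change grade, and one of the other shifts (skin damage of 5-9 mm) goes upward.

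A reader might also infer that redness and swelling cannot be graded at all. That is true only of the diary. Staff assess local reactions at 30-45 minutes and in clinic at 1, 2 and 4 weeks after the first two vaccinations, and an examiner can judge a share of circumference and a colour by eye. Nothing says that a diary number is converted mechanically into a grade. This part of the objection stands, but it does not close the gap. Under Risks the protocol expects local symptoms to last no more than several days. Its background reports that in a UK trial of another HIV DNA vaccine, local effects came mostly on the first day and resolved by 48 hours. A reaction gone by week 1 can no longer be measured.

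Three further limits stand:

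- Severe skin damage needs full-thickness disruption as well as size, so a full-thickness ulcer of 22 mm recorded as 20 mm does not become a superficial lesion. It fails the severe size criterion, but depth still argues against moderate.
- The measuring sentence names thickening, redness or lump. Skin damage appears in its heading and check instruction. Crust appears only as an mm item on the card, so applying the rounding to crust is an inference.
- The three-volunteer suspension rule requires the investigator to judge the event related and clinically significant, so a diary value of 30 against 31 mm does not by itself set or miss it.

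**Conclusion.** The point holds in a limited form. Diary rounding can lower induration of 31-34 mm from severe to moderate and can never do the reverse. The same holds for the size part of skin damage at 21-24 mm and, if the rule is meant to reach it, for crust at 41-44 mm. Independently of rounding, diary redness and swelling are not on the Appendix C scale, so two named components of the first primary endpoint cannot be graded from the only scheduled size record between the 30-45 minute check and week 1. This second part is the more consequential.

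The number of severe events lost cannot be stated. The 12.5 points per volunteer is the arithmetic of any arm of 8, not an estimate of bias. The erythema thresholds rest on an assumed circumference, but the conclusion that one width has no fixed grade does not depend on the exact range. The change is worth making before data are collected because it is nearly free and removes a one-way error at the boundary of a primary endpoint.

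**What to change.** Record diary sizes in whole millimetres without rounding, and state explicitly that the instruction covers skin damage and crust or scar as well as induration and redness.

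Reconcile the redness and swelling items with Appendix C so that both documents use the same measure of extent. For example, the diary could ask for extent around the arm for both signs, with arm circumference noted when the skin-fold is measured, and colour for redness. Widest diameter plus circumference would not be enough, since the widest part may lie along the arm and gives no colour.

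The cost is a diary reprint, a tape measurement at visits already scheduled and slightly more recording effort for volunteers.

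As a separate drafting correction, the vomiting row of Appendix C carries nausea wording (its mild grade reads "Minimal nausea causing no interference with daily activities") and needs criteria of its own.

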**Directions for Oral Temperature**

You will be given a supply of 3M Tempa-DOT Disposable Thermometers to use for recording your temperature on Day 1, 2 and 3 after each vaccination.

1. Wait at least 15 minutes before taking your temperature after exposure to cold weather, smoking, eating or drinking.
2. Place thermometer under tongue as far back as possible with dots facing either up or down.
3. Press tongue down on thermometer and keep mouth closed for 60 seconds.
4. Remove thermometer. Wait 10 seconds. Some dots may disappear as device locks in for accuracy.
5. Read the last blue dot. Ignore any skipped dot. Record temperature on the diary card.

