- Review interim medical history (including concomitant medications)
- Review safety laboratory data
- Review the informed consent form administered at screening visit with volunteer
- Perform a directed physical examination including vital signs (pulse, respiratory rate, blood pressure and temperature) as well as an assessment of axillary lymph nodes and any further examination indicated by history or observation
- Conduct pre HIV-test counseling
- Perform a skin-fold measurement of the upper arm (Appendix B)
- Collect blood and urine specimens for all tests as indicated in the Schedule of Procedures (Appendix A)
- Perform a pregnancy test for all female volunteers (blood will be sent stat)and obtain results prior to vaccination
- Perform baseline assessment of the site of injection and evaluate and record any systemic symptoms
- Administer vaccine (the preferred site of administration is the deltoid muscle of the upper arm) either by standard intramuscular injection or by electroporation. Depending upon the amount of adipose tissue at injection site, the length and gauge of the standard intramuscular needle and the gauge of the electroporation device will be adjusted (Appendix B)

Volunteers will be closely observed for at least 30 – 45 minutes after vaccination. Vital signs (pulse, respiratory rate, blood pressure and temperature) will be monitored at 30 – 45 minutes after vaccination and recorded. Any local and systemic reactogenicity events, as well as any other event that occurs, will be recorded at 30 – 45 minutes. At this time, subjects will also be asked to complete a Vaccine Tolerability Assessment Form (Appendix D). Furthermore, volunteers will be given a diary card (Appendix E) and asked to record any reactogenicity events that occur between Day 1 and Day 7 and Day 57 and Day 64, as well as Day 253 and Day 260 in those volunteers in the high dose EP group who elect to receive a third vaccination. Site staff will explain to the volunteer how to record reactogenicity events.

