**d) Primary Endpoints**

**Safety and Tolerability**:

- Severe local reactogenicity events (pain, tenderness, erythema/skin discoloration, edema, damage [vesiculation/ulceration], induration, formation of a crust or scab.
- Severe systemic reactogenicity events (fever, chills, headache, nausea, vomiting, malaise, myalgia, arthralgia, rash).
- Severe other adverse events (including laboratory abnormalities).
- All Serious Adverse Events.
- Proportion of volunteers with mild and moderate local and systemic reactogenicity events.
- Electroporation Tolerability Assessment Questionnaire Responses (Appendix B)

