**APPENDIX A: SCHEDULE OF PROCEDURES**

| Visit Day (D)/Week (W) | Screen D – 42 | D  0 | **D3 Phone | Wk 1 | Wk 2 | Wk4 | Wk  8 | D 59  Phone | Wk 9 | Wk  10 | Wk  12 | Wk  16 | Wk  24 | Wk 36 | D 255 Phone+ | Wk 37+ | Wk 38+ | Wk  40 | Wk 44+ | | Wk  48 | | Wk  56 |
| --- | --- | --- | --- | --- | --- | --- | --- | --- | --- | --- | --- | --- | --- | --- | --- | --- | --- | --- | --- | --- | --- | --- | --- |
| Visit Windows  ( Days) |  |  | 2 | 2 | 2 | 4 | 4 | 2 | 2 | 2 | 4 | 7 | 7 | 7 | 2 | 2 | 4 | 7 | 7 | 7 | | 7 | |
| Informed Consent | **X** |  |  |  |  |  |  |  |  |  |  |  |  |  |  |  |  |  |  |  | |  | |
| ADVAX Vaccine |  | **X** |  |  |  |  | **X** |  |  |  |  |  |  | **X+** |  |  |  |  |  |  | |  | |
| Medical History | **X** | **X** |  | **X** | **X** | **X** | **X** |  | **X** | **X** | **X** | **X** | **X** | **X** |  | **X+** | **X+** | **X+** | **X+** | **X** | | **X** | |
| General Physical Exam | **X** |  |  |  |  |  |  |  |  |  |  |  |  |  |  |  |  |  |  |  | |  | |
| Directed Physical Exam |  | **X** |  |  |  | **X** | **X** |  |  |  | **X** |  | **X** | **X** |  |  | **X+** | **X+** | **X+** | **X** | | **X** | |
| Pregnancy Test (women) | **X** | **X** |  | **X** | **X** | **X** | **X** |  | **X** | **X** | **X** | **X** | **X** | **X** |  | **X+** | **X+** | **X+** | **X+** | **X** | | **X** | |
| Pregnancy Avoidance Counseling | **X** | **X** |  | **X** | **X** | **X** | **X** |  | **X** | **X** | **X** | **X** | **X** | **X** |  | **X+** | **X+** | **X+** | **X+** | **X** | | **X** | |
| Risk Reduction and Safe Sex Counseling | **X** | **X** |  | **X** | **X** | **X** | **X** |  | **X** | **X** | **X** | **X** | **X** | **X** |  | **X+** | **X+** | **X+** | **X+** | **X** | | **X** | |
| HIV Testing (ref 11.1) Pre-/Post HIV test Counseling b | **X** | **X** |  |  |  | **X** | **X** |  |  |  | **X** |  | **X** | **X** |  |  |  |  |  | **X** | | **X** | |
| Adverse Events |  | **X** | **X** | **X** | **X** | **X** | **X** | **X** | **X** | **X** | **X** | **X** | **X** | **X** | **X+** | **X+** | **X+** | **X+** | **X+** | **X** | | **X** | |
| Serious Adverse Events |  | **X** | **X** | **X** | **X** | **X** | **X** | **X** | **X** | **X** | **X** | **X** | **X** | **X** | **X+** | **X+** | **X+** | **X+** | **X+** | **X** | | **X** | |
| Vital Signs (pre and 30-45 minute post vaccination) |  | **X** |  |  |  |  | **X** |  |  |  |  |  |  | **X+** |  |  |  |  |  |  | |  | |

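### The diary card tells volunteers to measure temperature and injection-site reactions on Days 1–3 only, while the protocol text and the card's own grid call for about a week of recording

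*Protocol*

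**What the plan says.** The protocol gives two different sets of measuring days.

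**Recording window.** Under Vaccination Visits, volunteers are "asked to record any reactogenicity events that occur between Day 1 and Day 7 and Day 57 and Day 64". A third window, Days 253–260, applies to anyone in the high-dose electroporation group who takes the optional third dose.

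**Card grid.** The Volunteer Diary Card has seven date columns. The temperature row reads "Measure before midnight of the date stated | °F | °F | °F | °F | °F | °F | °F". The rows for redness, skin damage, induration and crust or scab are also marked for measurement, with a millimetre cell under every date.

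**Card directions.** The page on measuring the injection site has volunteers look for induration, redness and skin damage "at injection site on Day 1, 2 and 3 after each injection", and then "use the measuring tape provided to measure the WIDEST part of the response on Days 1, 2, and 3". The Directions for Oral Temperature supply thermometers "to use for recording your temperature on Day 1, 2 and 3 after each vaccination".

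**Card lead sentence.** It asks for a severity rating of symptoms that last past 72 hours. It does not mention symptoms that begin after that point.

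**Endpoint.** Section d) lists severe local and systemic reactogenicity as primary, with fever, erythema, skin damage and induration among the named terms. It adds "Proportion of volunteers with mild and moderate local and systemic reactogenicity events".

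**The concern.** Appendix C grades fever by measured temperature, and induration and skin damage by size in centimetres. If no reading is taken, the grade cannot be assigned reliably. Two volunteers with the same reaction could leave different records, depending on whether each followed the grid or the directions.

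At stake are late or symptomless fever, the peak size of a lesion between Day 3 and the next clinic visit, and any reaction that starts after Day 3 and has gone by that visit. The section on risks says that electroporation may make local reactions more frequent or more severe, so this is the part of the safety profile the trial most needs to describe. The grades also feed the listing of grade 2 or higher events sent to the DSMB before escalation, and the count of severe events that suspends the trial.

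**Working it through.** The protocol states no figure to reproduce here. The check is a day count, followed by a look at what else could supply the missing readings.

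**Day count.** Inputs are the recording windows from Vaccination Visits, dosing on Day 0, Day 56 (8 × 7) and Day 252 (36 × 7), and instructed measurement on post-dose Days 1, 2 and 3.

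- Dose 1: the window has 7 days. 7 − 3 = 4 days without an instructed measurement (Days 4–7).
- Dose 2: Days 57–64 are post-dose Days 1–8, which is 8 days. 8 − 3 = 5 (Days 4–8).
- Optional dose 3: Days 253–260 are post-dose Days 1–8, again 8 days. 8 − 3 = 5.

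If the volunteer fills the grid instead, 7 − 7 = 0 days are uncovered after dose 1. After doses 2 and 3, the seven-column card is one column short of the eight-day window (8 − 7 = 1).

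**Other sources of a reading.**

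- *Temperature.* In Appendix A the row "Vital Signs (pre and 30-45 minute post vaccination") is marked only at Day 0, Week 8 and optional Week 36. Weeks 1, 9 and 37 have neither vital signs nor a directed examination. The Post-Vaccination Visits section adds an examination at those visits only when symptoms are present. The telephone call, 1 to 4 days after the dose, cannot recover a temperature that was not taken.
- *Lesions.* Staff assess reactogenicity at Weeks 1, 9 and 37, so a reaction that lasts until then is seen. Its earlier peak size is not, nor is one that has already resolved.
- *New onset.* The Vaccination Visits text covers any event in the window. The card's lead sentence does not clearly do so.

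**Which terms depend on a measurement.** Fever, induration and skin damage do. Redness and edema are graded in Appendix C by share of arm circumference, so the millimetre entry does not set their grade. Crust or scab is a measured row, but the directions place no day limit on it.

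**How much could fall after Day 3.** The protocol gives no onset times for this vaccine with electroporation, so what follows is assumption. Take the dose 1 window of 7 days. If onset is even, the share starting on Days 4–7 is 4/7 = 57%. If the daily onset rate decays exponentially with scale *s* days, the share is (e^(−3/s) − e^(−7/s)) / (1 − e^(−7/s)):

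- s = 3: (0.3679 − 0.0970) / 0.9030 = 30%
- s = 2: (0.2231 − 0.0302) / 0.9698 = 20%
- s = 1: (0.0498 − 0.0009) / 0.9991 = 5%

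These are shares of onsets that fall on days with no instructed measurement. The share actually lost would be lower, because some volunteers will fill the grid and some events will be reported at visits.

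**The case against.** A reader might infer that temperature and lesion size are measured on Days 1–3 only, so that the endpoint is unmeasured for the rest of the window. The documents do not support that. The grid carries measurement cells under every one of its seven dates, which is a competing instruction to measure daily. Staff are to explain to volunteers how to record events, they assess reactogenicity at Weeks 1, 9 and 37, and they ask about adverse events at each visit. The card also gives an emergency number. A symptomatic fever on Day 5 has several routes into the record. What remains exposed is mainly the unnoticed fever, the actual reading and the peak size.

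A reader might also infer that blank days will count as event-free, or that 3 measured days out of 7 inflate a denominator by 7/3. Neither follows. The endpoint is a proportion of volunteers, so its denominator is volunteers and not days. No section says how blank diary days are handled, and that may properly sit in an analysis plan not shown here.

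On size, the section on human trials with DNA vaccines reports that, in the UK trial of another HIV DNA vaccine, local effects arose mostly on the first day after the dose and cleared by 48 hours, and systemic effects cleared within 1 to 3 days. This points to the low end of the range above. It is not decisive, because that vaccine was given without electroporation.

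Finally, every group gets the same card, so the instruction is not itself a source of difference between arms, and the analysis is declared exploratory and descriptive. All of these points stand as limits on the concern. None of them reconciles the directions with the window.

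**Conclusion.** The point holds as an internal contradiction. The measuring directions stop at Day 3, while the protocol text and the grid run to Day 7, or to post-dose Day 8 after doses 2 and 3. For a volunteer who follows the directions, 4 of 7 days after dose 1 and 5 of 8 after doses 2 and 3 have no measured temperature or lesion size. These counts assume dosing exactly on Days 0, 56 and 252.

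The consequence is a risk of missing or inconsistent later data for fever, induration and skin damage, with possible under-counting of late or symptomless fever and of peak lesion size. It is not a certain absence of data or a demonstrated bias. The share of onsets after Day 3 ranges from 5% to 57% across the onset assumptions tried. The one piece of timing evidence in the protocol favours the low end. The directions should be corrected, but the safety analysis is not invalid because of them.

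**What to change.** Reconcile the Vaccination Visits text, the card grid and the two pages of measuring directions so that they name the same days:

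- In both sets of directions, replace the three named days with every day of the recording window, for temperature and for injection-site checks.
- Supply enough thermometers for that number of days.
- Reword the lead sentence so that it covers any symptom on any day of the window, including one that begins after Day 3.
- Make the window the same length after each dose, or give the card an eighth column for doses 2 and 3.

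If three-day measurement is kept on purpose, say so in the protocol and report fever and measured lesion sizes as Day 1–3 results.

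The cost is a change of wording on the card, a few more disposable thermometers per dose and slightly more effort for volunteers.
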